## 8. Study Discontinuation Criteria

### 8.1. Discontinuation criteria per study subject

Discontinue the study in the following cases: If you discontinue the study, clarify the reason and fill out the registration form.

- 1) When the consent of the research subject (or the agent) is withdrawn
- 2) When undesirable events such as side effects occur
- 3) When the principal investigator and co-investigator deem it appropriate to discontinue the study for any other reason.

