#### 5.3. Clinical Research Outline

In the tDCS stimulation used in this study, it is difficult to blind the presence or absence of irritation because the patient feels discomfort in the scalp when the stimulation is actually performed. On the other hand, in order to eliminate the effects of wearing the tDCS device even in a state where no stimulation is performed (sham stimulation), evaluation is performed with sham stimulation and actual stimulation. In general, patients with Parkinson's disease have large motor fluctuations in symptoms due to drug therapy, so the patient's condition may vary depending on the timing of the examination. Therefore, when conducting a stimulation test, it is considered that an appropriate evaluation cannot be performed unless the sham stimulation and the actual stimulus are evaluated as a set.

In this study, we evaluated the efficacy and safety of SMA stimulation for sham stimulation in PART 1 and the efficacy and safety evaluation of M1 stimulation for sham stimulation in PART 2. Two tests will be conducted. In PART 1, participants will first practice various gait assessment without any intervention. Next, the tDCS device is worn on the head for 20 minutes in a resting state (sham stimulation: no actual stimulation), and then the device is removed and gait evaluation is performed. Thereafter, the tDCS device is attached again, SMA stimulation is actually performed at 2 mA for 20 minutes, and then the

device is removed and gait evaluation is performed. This is PART 1. At this point, a decision is made on whether or not to move to PART 2 in consideration of the patient's condition and the feasibility of gait evaluation for each patient. If it is judged that it is possible to migrate, the test of PART 2 will be conducted at an interval of at least 6 hours after the implementation of PART 1. In PART 2, as in PART 1, various gait evaluations are first practiced without any intervention, and then gait evaluation is performed after 20 minutes of sham stimulation with a tDCS device. After that, the tDCS device is attached again, and M1 stimulation is actually performed at 2 mA for 20 minutes, gait evaluation is performed, and PART 2 is completed.

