### [Rationale]

- 1) Transcranial direct current electrical stimulation may affect implantable medical devices and electronic devices such as deep brain stimulators, pacemakers, and defibrillators.
- 2) Transcranial direct current electrical stimulation may affect psychiatric problems such as clinically significant depression
- 3) If there is an injury or defect in the irritated part of the skull, it may cause stronger stimulation than planned.
- 4) Because it cannot be ruled out that transcranial direct current electrical stimulation can induce epileptic seizures
- 5) Since the possibility of interaction between transcranial direct current electrical stimulation and metal coils cannot be ruled out
- 6) Patients deemed unsuitable as subjects by the principal investigator are not included

## 6.3. Criteria for Transition to PART 2

When the principal investigator or co-investigator determines that there is no problem with the implementation of PART 2 after confirming the patient's general condition and the presence or absence of adverse events after PART 1

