### 10.3. Usage, dose, frequency, time required, etc.

First, practice of in front of 3 cm gait assessment without wearing the tDCS device and without doing anything. Next, the tDCS device is worn in a resting state for 20 minutes (sham stimulation), and then the device is removed and gait evaluation is performed. Thereafter, the tDCS device is attached again and cortical stimulation is actually performed at 2 mA for 20 minutes, and then the device is removed and gait evaluation is performed. These two evaluations will be one session, and the same evaluation will be performed at different stimulation sites at intervals of 6 hours or more. The stimulation site is the supplementary motor cortex (SMA) in the first (PART1) and the second (PART2) is the primary motor cortex (M1). The duration of one test is about 1 hour.

In the case of patients with Parkinson's disease with large motor fluctuations, evaluation should be performed in a state where the drug is off (that is, when the symptoms are severe after the drug wears

off, that is, Parkinson's symptoms are noticeable). However, there is no discontinuation of the medication that is actually being taken.

10.4. Guidelines for stimulation increase and decrease, etc.

The intensity and duration of stimulation should be constant, but if the stimulus is unpleasant, the stimulation intensity will be reduced.

11. Concomitant medications and concomitant therapies

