##### 14.2. Predicted diseases, etc.

Study subjects may experience discomfort such as tingling, itching, headache, or burning sensation on the scalp where the irritation is being applied. In addition, there is a possibility of bruises and fractures due to falls during gait evaluation.

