#### 14.7. Remedies

##### 14.7.1. Delivery of salvage drugs, methods of treatment

If the study subject complains of discomfort such as itching, headache, or burning, the stimulation should be stopped immediately.

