### 19.3. Anticipated Dangers and Disadvantages and Measures to Minimize Them

Transcranial direct current electrical stimulation is based on the recommendation from the committee of the Japanese Society of Clinical Neurophysiology that stimulation at an intensity of 3 mA for up to 30 minutes is safe, and stimulation is performed within this range. In fact, the stimulator used in this study is actually a commercially available device, and the maximum output is 2.0 mA, and it is designed so that stimulation cannot be used for more than 20 minutes per day.

However, as an adverse event, it is expected to cause some tingling in the scalp. If the stimulus is unpleasant, respond by reducing the intensity of the stimulus. In addition, if the subject complains of discomfort such as itching, headache, or burning, the stimulation should be stopped immediately.

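### Section 8.1(2) withdraws a subject for any side effect, although the protocol expects scalp discomfort under real current and elsewhere has such patients continue

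*Protocol*

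**What the plan says.** **Withdrawal.** Section 8.1 opens with an instruction, "Discontinue the study in the following cases", and its second item reads "When undesirable events such as side effects occur". It sets no grade, seriousness or expectedness threshold. The third item depends on the investigators' judgement; the second does not.

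**Expected reaction.** Section 5.3 explains why blinding is difficult: "the patient feels discomfort in the scalp when the stimulation is actually performed". Section 9.1 names some scalp tingling as an expected side effect. Section 14.2 adds: "Study subjects may experience discomfort such as tingling, itching, headache, or burning sensation on the scalp".

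**Reduce.** Section 10.4: "if the stimulus is unpleasant, the stimulation intensity will be reduced". Section 19.3 repeats this: "If the stimulus is unpleasant, respond by reducing the intensity of the stimulus".

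**Stop.** Section 14.7.1: "If the study subject complains of discomfort such as itching, headache, or burning, the stimulation should be stopped immediately". Section 19.3 repeats this rule straight after the reduction rule.

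**PART 2.** Under section 6.3 the patient moves on if the investigator, having checked general condition and adverse events after PART 1, finds that "there is no problem with the implementation of PART 2".

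**Analysis.** Section 15.2 adopts the intention-to-treat principle with two exclusions: failure to meet the inclusion criteria, and never having been measured with a device. Section 15.3 analyses the within-patient difference between real and sham. Section 15.4 leaves out cases whose tests could not be performed, does not in principle impute, and refers the handling of missing values to the statistical analysis plan.

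**The concern.** The reaction that the protocol predicts from real current meets the wording of 8.1(2). Staff who follow that item withdraw a patient whom 10.4 would keep at lower intensity and whom 6.3 would allow into PART 2. The same event can therefore lead to different handling, depending on which section is followed.

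For the analysis, what matters is which patients would be lost. Sham passes no current, so a current-related reaction can arise only in the real session. If patients are withdrawn for it, those remaining are selected for tolerating the stimulation, and PART 2 is selected again. The primary comparison would then describe tolerant patients and not all those enrolled.

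**Working it through.** The protocol states no figure that could be reproduced here. The target of 20 comes from feasibility (section 15.1), with no alpha, power, effect, SD or intolerance rate. The check is a comparison of the text, followed by an illustration.

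**Step 1: does the expected reaction meet 8.1(2)?** Section 9.1 calls tingling a side effect. Section 8.1(2) names side effects and sets no threshold. By its wording, yes.

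**Step 2: can the other rules operate alongside it?**
- 8.1(2) against 10.4 and the reduction rule in 19.3: leaving the study and continuing at lower intensity exclude each other. This is a contradiction.
- 8.1(2) against 6.3: if any side effect ends participation, little is left for the investigator to decide after reviewing adverse events. This is a contradiction for patients with an expected reaction.
- 8.1(2) against 14.7.1: stopping a session and leaving the study are different levels of action and can both happen. There is no contradiction in itself.
- Reduce against stop: the first is triggered by an unpleasant stimulus, the second by discomfort with itching, headache or burning as examples. Section 14.2 groups those three with tingling under discomfort. The boundary is undefined.

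**Step 3: what is lost?** Within each PART the order is sham, walk, real stimulation, walk (section 5.3).
- Withdrawn before the second walk of PART 1: the PART 1 pair and all of PART 2 are lost.
- Withdrawn after that walk: the PART 1 pair is complete and PART 2 is lost.

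Because the analysis is paired, a missing real-session walk removes the whole pair. It does not leave one condition with fewer patients than the other.

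**Step 4: illustration.** Let q be the proportion withdrawn before the walk in each real session. The documents do not give q, so the values below are assumptions.

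- PART 1 pairs = 20(1 − q); PART 2 pairs = 20(1 − q)², if the same q applies again and there is no other loss.
- 95% confidence interval half-width, in SDs of the paired difference = t(0.975, n − 1)/√n.

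| q (assumed) | PART 1 pairs | PART 1 half-width | PART 2 pairs |
|---|---|---|---|
| 0% | 20 | 2.093/√20 = 0.468 | 20 |
| 10% | 18 | 2.110/√18 = 0.497 | 20 × 0.81 = 16.2 |
| 25% | 15 | 2.145/√15 = 0.554 | 20 × 0.5625 = 11.25 |
| 50% | 10 | 2.262/√10 = 0.715 | 20 × 0.25 = 5 |

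These figures show only the loss of precision. They do not measure the selection, whose direction and size the documents do not allow one to estimate.

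**The case against.** The strongest defence is that the protocol as a whole plainly expects patients with events to carry on. Section 6.3 reviews adverse events before PART 2, and the schedule in 12.1 records them in PART 1, at the transition and in PART 2. Section 15.2 already keeps all cases apart from its two exclusions, so a patient whose current was reduced or stopped and who then walked is not excluded. Handling of missing values is referred to a statistical analysis plan that was not available for this review. All of this stands and limits the severity. It does not remove the contradiction: 8.1(2) remains an unqualified instruction, and no analysis plan can recover a walk that was never done.

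A reader might infer stronger things, which the documents do not support:
- *Three mutually incompatible rules.* Section 19.3 can be read as graded, with tingling leading to reduction and itching, headache or burning leading to a stop. That reading is open, though the boundary is not defined.
- *Nearly every patient would be discontinued.* This takes one clause alone, against 6.3 and the schedule. Section 14.2 also says only that discomfort may occur.
- *Section 15.4 drops discontinued patients.* It drops cases whose tests could not be performed. A withdrawn patient is affected only if the walk is missed, and 8.1 does not say whether it is.
- *Only the real session can trigger 8.1(2).* Section 14.2 also predicts injuries from falls during gait evaluation, which can happen after sham. Only current-related reactions are confined to the real session.
- *Sections 5.3 and 6.3 set conflicting conditions for PART 2.* Section 5.3 mentions the feasibility of gait evaluation, and 6.3 is less explicit but broad enough to include it.

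**Conclusion.** The point holds as an internal contradiction: 8.1(2) against 10.4, the reduction rule in 19.3, and 6.3, together with an undefined line between reducing and stopping. If 8.1(2) is followed before the post-stimulation walk, the PART 1 pair and all of PART 2 are lost for that patient, and the comparison is limited to those who tolerated the current. This rests on withdrawal preceding the walk, which the protocol neither states nor rules out.

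The size is unknown because no intolerance rate is given. Under the assumed 25%, PART 1 falls to 15 pairs and the half-width rises from 0.47 to 0.55 SD, or by 0.554/0.468 − 1 = 18%. The study is exploratory and its target was not based on power, so this is an illustration and not the basis for the rating. It should be fixed, but it does not by itself invalidate the plan.

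**What to change.** 1. Reconcile sections 8.1(2), 10.4, 14.7.1, 19.3 and 6.3, so that each kind of event leads to one stated action and one stated consequence for PART 2. Which clinical rule applies is for the investigators to decide.
2. In sections 15.2 and 15.4, in line with the intention-to-treat principle already there, state that reduced or stopped stimulation is not in itself a reason to omit a patient, and that any post-stimulation gait data obtained are analysed under real stimulation.
3. Record the intensity and minutes actually delivered in each real session.

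The cost is protocol wording and two case report form fields. The drawback is a slight dilution of the estimated effect, because some analysed patients will have received less than the planned stimulation. The recorded intensity and minutes would let that be described.

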### 8.2. Discontinuation criteria for the entire clinical study

In the following cases, the entire study will be discontinued. In the event that the study is discontinued, the investigator shall promptly notify the study subject of the discontinuation and take other necessary measures to provide appropriate medical care. When the principal investigator discontinues the research, the principal investigator shall report the discontinuation, the reason, and a summary of the results in writing to the hospital director without delay.

- 1) When the Accredited Clinical Research Review Board determines that the research should not be continued.
- 2) If there is any doubt about the safety of the study
- 3) When facts or information are obtained that impair the ethical validity or scientific validity of the research
- 4) When information or facts are obtained that undermine the appropriateness of the conduct of the research or the credibility of the results

## 9. Treatment/Intervention for Clinical Study Subjects

### 9.1. Overview of Pharmaceuticals Used in Clinical Research

#### Transcranial Direct Current Electrical Stimulator (tDCS Instrument)

Brand name : Halo Sport 2

manufacturer : Halo Neuroscience

**Overview** : It is a commercially available headphone-type tDCS device. Three pairs of stimulation pads are attached, which are attached to the crown of the head (M1). The midline pad is on the upper and lower limbs on both the left and right sides, as well as the trunk. The pads on both sides are designed to perform anode stimulation in the left and right hand finger areas. Originally for athlete training and musical instrumentsIt is a device developed to improve skills, has a maximum output of 2.0 mA, and is operated with a smartphone application.1timeIt is designed so that stimulation cannot be done for more than 20 minutes.In addition, it is small and lightweight, and it is possible to stimulate the patient while actually walking.

In this study, with normal attachment to the crown of the head, stimulation from the midline pad M1 stimulation of the upper and lower limbs on both sides and the trunk is possible, and from that state both sides SMA stimulation is possible by shifting in front of 3 cm around the coronal suture. In sham stimulation, All you have to do is attach the device to each part. It doesn't actually stimulate.

**Significant side effects:** This device is actually a commercially available tDCS device, which is widely used by the general public, and its safety is ensured by the design of the stimulator. Stimulation with this device is performed within the scope of the recommendation from the committee of the Japanese Society of Clinical Neurophysiology that stimulation at an intensity of 3 mA for up to 30 minutes is safe, so it is unlikely to cause serious side effects. However, as a side effect, it is expected that you will feel some tingling in the scalp.

[figure not shown]

Halo Sport 2

## 10. Procedures for administering interventions such as medication, surgery, and tests

### 10.1. Medication site, surgery site, examination site, etc.

The stimulation sites are the scalp on the supplementary motor cortex (SMA) and the primary motor cortex (M1), respectively, for sham stimulation and actual stimulation.

[figure not shown]

### 10.2. Timing and duration of interventions such as medication, surgery, and examinations

After this registration, 2 sets of walking evaluations will be performed in 1 to 2 days (2 walking evaluations in PART 1 and 2 walking evaluations in PART 2, 4 times in total). After the first set of walking evaluations, there will be a wash out period of at least 6 hours.

### 10.3. Usage, dose, frequency, time required, etc.

First, practice of in front of 3 cm gait assessment without wearing the tDCS device and without doing anything. Next, the tDCS device is worn in a resting state for 20 minutes (sham stimulation), and then the device is removed and gait evaluation is performed. Thereafter, the tDCS device is attached again and cortical stimulation is actually performed at 2 mA for 20 minutes, and then the device is removed and gait evaluation is performed. These two evaluations will be one session, and the same evaluation will be performed at different stimulation sites at intervals of 6 hours or more. The stimulation site is the supplementary motor cortex (SMA) in the first (PART1) and the second (PART2) is the primary motor cortex (M1). The duration of one test is about 1 hour.

In the case of patients with Parkinson's disease with large motor fluctuations, evaluation should be performed in a state where the drug is off (that is, when the symptoms are severe after the drug wears

off, that is, Parkinson's symptoms are noticeable). However, there is no discontinuation of the medication that is actually being taken.

10.4. Guidelines for stimulation increase and decrease, etc.

The intensity and duration of stimulation should be constant, but if the stimulus is unpleasant, the stimulation intensity will be reduced.

11. Concomitant medications and concomitant therapies

11.1. Concomitant Prohibited Drugs and Prohibited Therapies

There is no specific prohibition of concomitant drugs.

11.2. Concomitant drugs and therapies

All medications for the disease are possible, and there is no discontinuation of the medication that is actually being taken.

12. Observation and inspection items, implementation timing, and data collection method

12.1. Observation and Inspection Schedule

| Implementation Period                             |                                              | Screening period | Evaluation period                  |                                        |                                                       |
|---------------------------------------------------|----------------------------------------------|------------------|------------------------------------|----------------------------------------|-------------------------------------------------------|
|                                                   |                                              |                  | PART 1                             | Decision to move to PART 2             | PART 2                                                |
| Time of implementation                            |                                              |                  | Anytime after the end of screening | Within 6 hours after the end of PART 1 | More than 6 hours have passed since the end of PART 1 |
| Confirmation of basic subject information         |                                              | ○                |                                    |                                        |                                                       |
| Verify eligibility                                |                                              | ○                |                                    | ○                                      |                                                       |
| Obtaining Consent                                 |                                              | ○                |                                    |                                        |                                                       |
| MDS-UPDRS                                         |                                              | ○                |                                    |                                        |                                                       |
| Cognitive Function Assessment (MMSE, FAB, MoCA-J) |                                              | ○                |                                    |                                        |                                                       |
| Quality of Life Assessment (PDQ-39)               |                                              | ○                |                                    |                                        |                                                       |
| Evaluation of Footfall (FOG-Q)                    |                                              | ○                |                                    |                                        |                                                       |
| Sham stimulation / SMA stimulation                |                                              |                  | ○                                  |                                        |                                                       |
| After Sham stimulation / After SMA stimulation    | Walking distance in 30 seconds               |                  | ○                                  |                                        |                                                       |
|                                                   | 10m Natural Walking Time and Number of Steps |                  | ○                                  |                                        |                                                       |
|                                                   | Timed Up and Go test                         |                  | ○                                  |                                        |                                                       |
|                                                   | 360° rotation test                           |                  | ○                                  |                                        |                                                       |
|                                                   | Video recording of walking                   |                  | ○                                  |                                        |                                                       |

|                                                  |                                              |  |   |   |   |
|--------------------------------------------------|----------------------------------------------|--|---|---|---|
|                                                  | conditions                                   |  |   |   |   |
| Sham stimulation / M1 stimulation                |                                              |  |   |   | ○ |
| After Sham stimulation /
After M1 stimulation | Walking distance in 30 seconds               |  |   |   | ○ |
|                                                  | 10m Natural Walking Time and Number of Steps |  |   |   | ○ |
|                                                  | Timed Up and Go test                         |  |   |   | ○ |
|                                                  | 360° rotation test                           |  |   |   | ○ |
|                                                  | Video recording of walking conditions        |  |   |   | ○ |
| Adverse Events and Defects                       |                                              |  | ○ | ○ | ○ |

\*Within 3 months after the end of screening (even if you are readmitted to the hospital after being discharged from the hospital)

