In addition, since previous studies have shown that the increase in cortical excitability by tDCS persists for up to 150 minutes after the end of stimulation, a sufficient washout period of at least 6 hours should be given before PART 1 is completely eliminated before PART 2 tests conduct.

[figure not shown]

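### An adverse-event check is scheduled after the SMA session but none after the M1 session, so the two sites' safety rests on unequal ascertainment

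*Protocol*

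**What the plan says.** The schedule in Protocol section 12.1 has a row "Adverse Events and Defects" with three marks: PART 1 (sham, then SMA stimulation), the decision to move to PART 2, and PART 2 (sham, then M1 stimulation). The decision column is timed "Within 6 hours after the end of PART 1". The PART 2 column is timed "More than 6 hours have passed since the end of PART 1". No column stands to the right of PART 2.

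Section 6.3 gives the content of the decision visit. The investigator decides on PART 2 "after confirming the patient's general condition and the presence or absence of adverse events after PART 1".

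Section 5.3 closes the second session in these words: "M1 stimulation is actually performed at 2 mA for 20 minutes, gait evaluation is performed, and PART 2 is completed". The same section states that the study evaluates efficacy and safety for SMA in PART 1 and for M1 in PART 2.

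Section 13.2 names adverse events and defects as the safety endpoint and gives no observation window. Section 15.3 reports a frequency and proportion for each adverse event, also without a window. Section 14.6 requires a report when the investigator learns of a disease during the study.

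**The concern.** Both sites are to be assessed for safety, but the schedule looks for events after only one of them. After SMA the investigator has to ask about adverse events at a separate visit. After M1 the last scheduled opportunity is the session itself. An event that begins once the patient has left the rehabilitation room, such as a headache or scalp discomfort (both listed as predicted in section 14.2), would be found by an active check after SMA if it had begun by then. After M1 it would reach the data only if someone volunteered it.

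At stake is how the adverse-event proportions are read. A lower count for M1 could reflect less asking rather than fewer events. No analysis plan can repair this afterwards, because events that nobody asked about are not in the data.

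**Working it through.** The protocol gives no figure to reproduce. The check sets the scheduled contacts side by side and then bounds the time observed after each stimulation.

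**Scheduled contacts after each active stimulation**

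| | After SMA (PART 1) | After M1 (PART 2) |
|---|---|---|
| Adverse-event mark in the session column (12.1) | yes | yes |
| Separate later check marked for adverse events (12.1, 6.3) | yes, at most 6 hours after PART 1 | none |
| Further scheduled contact | start of PART 2, more than 6 hours later | none |

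For a subject who completes both PARTs, that is two contacts after the SMA session and none after the M1 session. For a subject who stops after PART 1, it is one after SMA.

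**Time observed after stimulation**

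Inputs: section 10.3 says "The duration of one test is about 1 hour" and includes two wearing periods of 20 minutes each. I read one test as one whole session, which is an assumption.

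- Time left outside the wearing periods: 60 − 20 − 20 = about 20 minutes.
- This also has to hold the practice and the gait evaluation after sham, so scheduled observation after M1 is at most about 20 minutes.
- The check after SMA may fall at any time up to 6 × 60 = 360 minutes after PART 1 ends. Its latest possible reach after stimulation is about 20 + 360 = 380 minutes. Its earliest is directly after the SMA gait evaluation.

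The 20-minute bound depends on the reading of session length. The contact count does not.

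**Does another section close the gap?** Sections 13.2 and 15.3 set no window that would extend or equalise observation. Sections 12.2 and 12.3 list no adverse-event item and no collection method. Section 14.6 applies once the investigator knows of an event, so it is passive. Monitoring is central and takes place once, at the end of the study (17.1.1), so it cannot supply observations that were not made.

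**The case against.** The strongest reply is that the longer SMA window is a maximum, not a plan. Six hours is an upper limit, and section 5.3 places the decision at the close of PART 1, so the check could come straight after the SMA gait evaluation. This stands: it cannot be said that SMA events are followed for hours. But even an early check is a separate contact with an adverse-event question, the start of PART 2 brings another, and M1 has neither.

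Second, no section says that adverse-event recording stops when PART 2 is completed. Subjects are enrolled as inpatients (6.1) and the reporting duty in 14.6 runs through the study. This also stands in part. A reader might infer that late M1 events are lost; the text supports only that they can be missed, because unprompted reporting remains possible. It does not replace a scheduled question.

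Third, a reader might turn the statement that "the increase in cortical excitability by tDCS persists for up to 150 minutes after the end of stimulation" into a share of adverse events falling outside M1 observation, or subtract to get 150 − 20 = 130 unobserved minutes of risk. The protocol does not support that. The figure describes excitability and says nothing about when adverse events begin. Many of the events predicted in 14.2 would arise during stimulation or during the walking tests, where they would be seen.

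Fourth, a reader might expect an invalid SMA-versus-M1 safety test, or argue that a cumulative effect would show after the second stimulation. No such test is planned. The cumulative effect is conjecture, and the planned washout of at least 6 hours exceeds the stated after-effect. Neither belongs in the point.

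**Conclusion.** The point holds as an asymmetry in scheduled ascertainment. Followed as written, the protocol actively looks for adverse events after the SMA session and not after the M1 session, while section 5.3 makes the safety of each site an aim. Events that start after the M1 session can be missed unless reported spontaneously, and adverse-event proportions for the two sites would not rest on equal observation.

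The size that can be stated is two scheduled contacts after SMA (one if the subject does not enter PART 2) against none after M1. If one test means one session, at most about 20 minutes are observed after M1. The number of events affected cannot be estimated from the protocol. In an exploratory study of 20 patients this is not a fatal flaw, but it bears on a stated aim and is simple to correct before data are collected.

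**What to change.** Add to the section 12.1 schedule one adverse-event check after PART 2, matching the one after PART 1, and state the same time window for both checks. The present wording for the decision visit is only an upper limit, so copying it unchanged would still let the two checks fall at different times. The investigators should choose the length of the window; what matters here is that it is stated and equal.

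If this is not done, report adverse events by site only up to the end of each PART's gait evaluation, and say so in section 15.3.

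The cost is one schedule column, one form entry and one brief extra contact per subject. Because subjects are enrolled as inpatients, the burden is small. The one downside is a slightly later end of participation for a patient discharged the same day.
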